### Concomitant care permitted or prohibited during the trial {15d}

Participants will be encouraged to maintain routine inpatient activities such as ambulation and sitting in an armchair, and to perform, twice daily, breathing exercises (deep inspiration and diaphragmatic breathing), active free limb exercises and global stretching—standard unit interventions.

### Ancillary and post-trial care {34}

#### Immediately after study completion

Participants will continue to receive standard clinical care at Hospital São Paulo. Study participation consists of a single supervised exercise session and does not alter routine medical management. Following the exercise session, all participants will be encouraged to continue with standard inpatient cardiac rehabilitation.

#### After discharge from hospital

No specific study-related interventions beyond usual clinical care are planned after the study ends. Participants will follow routine post-hospitalization cardiac care in the outpatient setting.

#### Access to results

All participants will be informed about study results upon publication. Participants may request a summary of overall findings by contacting the research team ([contact]).

#### Special provision for control group

Participants randomized to the control group (exercise without VR) will be offered an opportunity to experience the VR device after study completion, as a gesture of appreciation and to provide them access to the innovative intervention they did not receive during the study.

#### Compensation for participation

Participants will not receive monetary compensation for study participation. All study procedures are provided at no cost to participants as part of routine inpatient care at Hospital São Paulo.

#### Harm compensation

##### If adverse effects occur

If any participant experiences harm or adverse effects related to study participation, appropriate medical support will be provided immediately by Hospital São Paulo clinical staff. Any injury occurring during the study exercise session will be managed according to standard institutional protocols.

#### Injury compensation and liability

Federal University of São Paulo (UNIFESP), as the sponsoring institution, maintains institutional liability coverage.Participants retain all legal rights under Brazilian law to seek compensation if harm occurs.Serious adverse events will be reported to the Research Ethics Committee for evaluation.

### Outcomes {16}

#### Primary outcome

Influence of VR on tolerance to cycle-ergometer aerobic exercise in hospitalized patients with HF. The primary endpoint is effective exercise time (minutes), defined as total session duration until interruption due to physical limitations or symptoms, comparing VR vs. no-VR.

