**Methods:**

We will conduct a randomized, controlled, parallel-group trial with 1:1 allocation. Adult inpatients with a diagnosis of HF will be screened for eligibility and randomly assigned to two groups: control (cycle-ergometer aerobic exercise) and intervention (the same exercise combined with an Meta Quest 2 VR device). Each participant will complete a single session of up to 20 min, consisting of five blocks of 3 min of continuous pedaling interspersed with one-minute passive rests, with early termination in case of intolerance. The primary outcome is effective exercise time (minutes) until interruption due to physical limitation or symptoms. Secondary outcomes include rating of perceived exertion, hemodynamic parameters, exercise enjoyment (PACES) and usability of the technology (SUS, intervention group only).

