Virtual reality (VR) has emerged as a promising technology to enhance CR engagement and adherence. Unlike conventional CR methods, which may be repetitive and less engaging, VR systems enable enjoyable activities with therapeutic purpose and interaction with virtual environments tailored to rehabilitation needs [11, 12]. VR is hypothesized to enhance engagement and adherence through several interconnected psychological and physiological mechanisms: (1) immersive environments reduce perceived exertion and distract from unpleasant physical sensations [13]; (2) VR fulfils core psychological needs (autonomy, competence, relatedness) as described by Self-Determination Theory [14]; (3) gamified elements and real-time feedback activate brain reward systems, promoting self-efficacy and behavioral persistence [15]; and (4) immersive experiences significantly reduce anxiety while improving mood states, which may enhance willingness to participate in rehabilitation [12, 16]. These mechanisms suggest that VR may be particularly valuable for acutely hospitalized HF patients, who often experience high exercise-related anxiety, low motivation and multiple barriers to traditional rehabilitation.

Preliminary evidence from our pilot study [17] demonstrated the feasibility of immersive VR exercise in hospitalized HF patients, with participants reporting enjoyment (Physical Activity Enjoyment Scale scores). However, rigorous evidence from a randomized controlled trial is needed to establish definitive clinical efficacy and justify broader implementation.

This trial aims to rigorously evaluate the efficacy of immersive VR aerobic exercise in enhancing exercise tolerance and patient satisfaction in hospitalized HF patients. Primary objective: To compare total exercise time between VR and standard cycle ergometer exercise. Secondary objectives: To assess between-group differences in perceived enjoyment (PACES) [18, 19], and system usability (SUS) [20, 21], as well as physiological responses.

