#### Secondary outcomes

Exercise time and clinical parameters (systolic/diastolic blood pressure, respiratory rate, peripheral oxygen saturation, heart rate and rating of perceived exertion) during cycle-ergometer exercise with and without VR. These parameters will be measured across the exercise session, comparing the two approaches.Usability of the VR system during exercise, assessed using the System Usability Scale (SUS) [11, 12] administered after the session (intervention group): ease of use, comfort and perceived immersion.Patient satisfaction with the exercise experience, comparing sessions with and without VR, measured using the Physical Activity Enjoyment Scale (PACES) [13, 14].

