**POST-EXERCISE ASSESSMENTS**				
Total exercise time (minutes) (g)				X
Recovery vital signs				X
SUS—VR group only (i)				X
PACES (h)				X
Adverse events assessment (j,k)				X

a) Single-session design: Only ONE exercise session per participant during hospitalization.

b) Timepoints: Enrollment → Randomization → Intervention → Post-Exercise/Close-Out. No follow-up.

c) Both groups identical protocol except: VR group receives immersive VR headset; control group receives standard cycle ergometer.

d) Hospital Anxiety and Depression Scale (HADS): 14-item self-report questionnaire assessing anxiety (7 items, score 0–21) and depression (7 items, score 0–21) during acute hospitalization [24, 25]

e) Continuous vital signs monitoring: Blood pressure (BP, mmHg, systolic/diastolic), heart rate (HR, bpm), peripheral oxygen saturation (SpO₂, %) and respiratory rate (RR, breaths/min) recorded every minute throughout exercise and recovery period via automated monitors and continuous 12-lead ECG.

f) Session termination criteria: Immediate termination triggered if Rating of Perceived Exertion (RPE) ≥ 5 (‘hard’ intensity) OR if any safety threshold exceeded: BP > 200 mmHg or < 80 mmHg (systolic), HR > 130 or < 40 bpm,SpO₂ < 85% or ST-segment changes on ECG.

g) Total exercise time: Cumulative pedaling time (minutes) from initiation to termination.

h) Physical Activity Enjoyment Scale (PACES): 18-item questionnaire (score 18–80); higher = greater enjoyment [18, 19]

i) System Usability Scale (SUS10-item questionnaire (score 0–100); ≥ 68 indicates above-average usability; ≥ 70 considered acceptable for clinical implementation [20, 21]

j) Adverse events: Serious (requiring intervention) vs. non-serious. Documented immediately post-exercise.

k) Real-time data collection: All vital signs, RPE, observations recorded by physiotherapist on paper CRF during exercise; transferred to REDCap same day.

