#### Who will be included in each analysis {27b}

All randomized participants who provided informed consent and were allocated to a group will be included in the primary intention-to-treat (ITT) analysis, according to their original allocation, regardless of adherence or protocol deviations. Secondary per-protocol analysis will include participants who completed the entire planned exercise session without unplanned termination due to participant request or safety concern. Analysis will be based on actual exercise duration achieved by each participant (measured continuously, independent of exercise structure). Results from per-protocol analysis will be compared with intention-to-treat findings to assess robustness of primary findings.

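### The primary endpoint has two conflicting definitions: session duration, which counts the passive rests, and cumulative pedalling time, which does not

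*Protocol article*

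**What the plan says.** All references are to the protocol article.

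- **Outcomes {16}, Primary outcome:** the endpoint is "effective exercise time (minutes), defined as total session duration until interruption" because of symptoms or physical limitation.
- **Participant timeline {18}, note g**, attached to the item collected after exercise: "Total exercise time: Cumulative pedaling time (minutes) from initiation to termination".
- **Background and rationale {9a}:** "Primary objective: To compare total exercise time between VR and standard cycle ergometer exercise". This is the term that note g defines.
- **Abstract, Methods:** the session consists of "five blocks of 3 min of continuous pedaling interspersed with one-minute passive rests", up to 20 min in all. The exercise protocol under {15a} gives the same upper limit.
- **Sample size {19}** and **Statistical methods {27a}** speak of total exercise duration and do not say whether rests count.
- **Who will be included in each analysis {27b}** uses actual exercise duration, "measured continuously, independent of exercise structure". It does not mention rests either.
- **Outcomes {16}, Secondary outcomes** opens with "Exercise time and clinical parameters", so time appears again outside the primary endpoint.

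**The concern.** The outcome is meant to measure tolerance of exercise and will be reported in minutes. On the Primary outcome wording, time spent sitting still between blocks is credited as tolerated exercise. On note g it is not. The same participant therefore has two legitimate scores, and the same trial has two legitimate treatment effects in minutes. Either could be reported without departing from the published text. A reader who wants to judge whether the gain is clinically worthwhile, or to pool it with other studies, would not know which quantity the number represents. Blinding the analyst to group labels does not settle which clock applies.

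**Working it through.** **Inputs from the article.** Five blocks of 3 min; 1-min passive rests between blocks; session limit 20 min; d = 0.65 with no difference or SD in minutes. Means, SDs and completion rates are not given, so those used below are assumptions.

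**1. The session limit.** Pedalling: 5 × 3 = 15 min. With rests only between blocks: 15 + 4 = 19 min. With a fifth rest after the last block: 15 + 5 = 20 min. So 20 is reproduced only with a fifth rest, although 19 also respects a limit of up to 20. Rest makes up 4/19 = 21% or 5/20 = 25% of a completed session.

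**2. From one clock to the other.** For a stop while pedalling at cumulative pedalling time P, session time is S = P + (⌈P/3⌉ − 1).

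| Stop | Pedalling clock (min) | Session clock (min) |
|---|---|---|
| In block 1 | 2 | 2 |
| In block 3 | 6.5 | 8.5 |
| End of block 3, block 4 declined | 9 | 11, up to 12 if declared at the end of the rest |
| In block 5 | 12.5 | 16.5 |
| Session completed | 15 | 19, or 20 with a fifth rest |

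Two participants one block apart, 6 and 9 min of pedalling, differ by 3 min on one clock and by 11 − 7 = 4 min on the other. Two who stop in the same block, at 4 and 5.5 min, differ by 1.5 min on both.

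**3. Effect on the group difference (assumed distributions).**

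- *Weibull stop times, shape 1.2, capped at 15 min.* For control/VR completion of 10/30%, 30/60% and 50/80%, the mean differences are 2.7, 2.8 and 2.4 min of pedalling and 3.5, 3.6 and 3.1 min of session. The session difference is 27% to 29% larger. Varying the shape (0.6 to 3) and completion (2/8% to 50/80%) widens this to 23% to 31%.
- *Normal stop times clipped at 15 min.* With control/VR means of 6–10/8–12 min and SD 3–4, differences of 1.8 to 2.4 min become 2.3 to 3.2 min. The increase is 30% to 36%, the upper part arising when completers are credited with a fifth rest.
- *The range is not a bound.* In the 50/80% Weibull case, crediting completers with a fifth rest adds (0.80 − 0.50) × 1 = 0.30 min. That gives about 3.1 + 0.3 = 3.4 against 2.4 min, roughly 40% larger.

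**4. Effect on the test.** Numerator and SD grow together. In the three main Weibull cases d is 0.56 to 0.58 on pedalling time and 0.55 to 0.57 on session time; under the normal assumptions it moves by about 0.005 at most. The map in step 2 is strictly increasing, so ranks are preserved and the Mann–Whitney p-value is identical. In simulated trials with 30 per arm the t-test decision differed in only about 1% to 1.5%.

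**5. Effect on the sample size.** None, because it was computed from a unitless d. Whether the stated 30 per group follows from its own inputs is a separate question that does not depend on the clock.

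**The case against.** The strongest reply is that the intended clock can be inferred and that the choice cannot change the trial's conclusion.

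**Intent.** The label in the Primary outcome section is effective exercise time, the primary objective uses the term that note g defines, and {19} and {27a} speak of exercise duration rather than session duration. On this reading the phrase about session duration is the outlier. That is fair, and it supports choosing pedalling time. It does not remove the conflict: the outlier is the formal definition of the primary endpoint, and nothing overrides it.

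**Consequence.** A reader might infer that picking a clock after seeing the data could make or break superiority, or that power is affected. The working does not support this. Under non-normality {27a} moves to Mann–Whitney, where the clocks agree, and the t test almost never changes its decision. The one exception is small: participants who stop during the same rest tie on pedalling time and can be ordered on session time.

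Three further readings also go beyond the text:

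- **{27b} as a second session-clock definition.** Its wording may mean only that time is recorded on a continuous scale and not as whole blocks completed.
- **A second version of time among the secondary outcomes.** The entry may be simple duplication; nothing shows that a different variable is intended.
- **The 20-min figure as an error.** It is an upper limit that 19 min satisfies, a fifth rest may be intended, and the session schematic (Fig. 1) is not reproduced in the text reviewed.

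**Conclusion.** The point holds. The Primary outcome section and note g define the same quantity in incompatible ways, and no other section reconciles them. This is a contradiction in the text, not a detail left to an analysis plan. Completers score 15 or 19 to 20 min, which follows from the schedule alone. The inflation of the group difference on the session clock, about 23% to 36%, rests on assumed stop-time distributions; it shrinks towards zero if most participants stop in block 1 and can exceed that range if many complete and a fifth rest is credited. The harm is confined to what the reported minutes mean and how large they look. The superiority test and the planned number of participants are essentially unaffected.

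**What to change.** - Amend the Primary outcome definition to agree with note g: cumulative pedalling time in minutes, rests excluded, range 0 to 15 min. A stop declared during a rest scores the pedalling time already completed.
- Use that one term in the Abstract, {19}, {27a} and {27b}, and state in {27b} that independence of exercise structure does not mean that rests are counted.
- In the secondary outcomes, either say that exercise time is the same variable as the primary endpoint or remove it.
- Reconcile the 20-min limit with five 3-min blocks and interspersed rests, so that the article says whether a rest follows the last block. Which schedule applies is for the investigators to state.

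The cost is a wording amendment, best made before outcome data are examined. Block start and stop times must be on the case report form, since the article does not say explicitly that they are recorded. The reported effect in minutes will look smaller than on the session clock.

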#### Secondary outcomes

Exercise time and clinical parameters (systolic/diastolic blood pressure, respiratory rate, peripheral oxygen saturation, heart rate and rating of perceived exertion) during cycle-ergometer exercise with and without VR. These parameters will be measured across the exercise session, comparing the two approaches.Usability of the VR system during exercise, assessed using the System Usability Scale (SUS) [11, 12] administered after the session (intervention group): ease of use, comfort and perceived immersion.Patient satisfaction with the exercise experience, comparing sessions with and without VR, measured using the Physical Activity Enjoyment Scale (PACES) [13, 14].

### Harms {17}

#### Anticipated harms and safety considerations

##### Exercise-related harms (applicable to both groups)

The primary anticipated harms relate to the physiological stress of exercise in hospitalized heart failure patients. These include:Cardiovascular events:Acute coronary syndrome symptoms (chest pain, dyspnea, diaphoresis)Dangerous arrhythmias (sustained ventricular tachycardia, rapid atrial fibrillation)Hemodynamic instability (acute hypotension, cardiogenic shock)Syncope or presyncopeRespiratory events:Severe dyspneaOxygen desaturation (SpO₂ < 85%)Musculoskeletal:Muscle crampsLeg pain or exacerbation of joint pain

#### VR-specific harms (intervention group only)

Cybersickness:Nausea or vomitingDizziness or vertigoDisorientationHeadache or eye strainDevice-related:Skin irritation from headset contactEquipment malfunction preventing safe use

#### Definition and assessment of harms

Expected harms are defined as adverse events anticipated based on:Physiological response to exercise in HF patientsKnown characteristics of VR technology in similar populationsLiterature reporting on exercise stress testing and cardiac rehabilitationUnexpected harms are defined as adverse events not anticipated or not mentioned in this protocol.

All harms will be assessed systematically through:Continuous monitoring during exercise:Real-time vital signs assessment (every minute)Continuous visual observationVerbal communication with participantStandardized questionnaires:Modified Borg Rating of Perceived Exertion (0–10 scale)—every minutePost-exercise symptom assessmentSystem Usability Scale (for VR-related issues in intervention group)Adverse event documentation:Type of adverse eventTiming (during exercise and during recovery)Severity classification (mild, moderate, severe)Relatedness to study procedures (definite, probable, possible, unrelated)Whether event required intervention/treatment

#### Harms classification and standardization

##### Severity classification

Mild: Uncomfortable but does not interfere with daily function; resolves spontaneously or with minimal interventionModerate: Interferes with daily function or requires medical intervention; may persistSevere: Incapacitating; requires hospitalization or prevents exercise continuation; potentially life-threatening

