#### Participant-initiated discontinuation

Perceived dyspnea or lower-limb fatigue ≥ 5 on Modified Borg Scale (indicating excessive effort)Participant requests to stop due to discomfort, inability to continue or any other reasonAdverse effects related to the VR device compromising well-being, requiring suspension

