#### Reporting approach for adverse events

All serious adverse events will be reported, defined as events requiring hospitalization, causing persistent incapacity, resulting in permanent disability or potentially life-threatening. All VR-related adverse events will be reported, defined as cybersickness symptoms (nausea, dizziness, disorientation, headache, eye strain) occurring during or immediately after study procedures. All exercise-stopping events will be reported, defined as any adverse event leading to early session termination before planned protocol completion. Adverse events occurring in ≥ 5% of participants in either group will be reported. Any adverse event causing permanent harm will be reported. Non-serious adverse events not meeting above criteria may be summarized descriptively but will not be listed individually in results.

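### On its plain reading, the Severe adverse-event grade takes in a brief symptom that merely ends the session, although the same event also fits the Mild grade

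*Protocol article*

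**What the plan says.** All places are in the protocol article.

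- **Severity classification.** Mild is discomfort that leaves daily function intact and settles by itself or with little help. Moderate interferes with daily function or needs medical treatment. Severe opens with incapacity and continues "requires hospitalization or prevents exercise continuation; potentially life-threatening". No rule covers an event that fits more than one grade.
- **Definition and assessment of harms.** One of the three grades is to be recorded for each adverse event.
- **Clinical manifestations** (discontinuation criteria, item 15b). Dizziness and pallor are among the findings that end exercise at once, with no intensity threshold.
- **Participant timeline, note f.** "Immediate termination triggered if Rating of Perceived Exertion (RPE) ≥ 5".
- **Reporting approach for adverse events.** Exercise-stopping events form their own category: "any adverse event leading to early session termination before planned protocol completion". Serious events are defined separately as "events requiring hospitalization, causing persistent incapacity, resulting in permanent disability or potentially life-threatening".
- **Primary outcome.** Effective exercise time is "total session duration until interruption due to physical limitations or symptoms".

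**The concern.** A severity grade should describe how intense an event was and what it led to. Here one route into the top grade is an operational fact, namely that pedalling stopped. This protocol deliberately stops exercise at a low threshold, so a passing symptom can end a session. Such an event would share a tier with incapacitating or life-threatening ones, or be called Mild, depending on which line the rater reads.

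Two things are at stake. First, raters can give opposite grades to the same event while both follow the text. Second, symptom-driven stopping also sets the primary endpoint, so a severity table could partly restate the efficacy result when read as safety information. Comparing safety between groups is a stated secondary objective.

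**Working it through.** The point concerns definitions, and the plan has no figure of its own to reproduce. The check sets the definitions side by side.

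**1. A test case.** A participant becomes dizzy, the session is ended as Clinical manifestations requires, and the dizziness clears within a minute of rest.

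| Grade | Descriptor | Met? |
|---|---|---|
| Mild | Discomfort, daily function intact, settles unaided | Yes |
| Moderate | Daily function affected, or treatment needed | No |
| Severe | Incapacitating | No |
| Severe | Needs hospital admission | No |
| Severe | Exercise cannot go on | Yes |
| Severe | Potentially life-threatening | No |

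With the Severe descriptors read as alternatives, the event fits the lowest and the highest grade but not the middle one.

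**2. The joint reading.** If all the Severe descriptors had to be met together, the dizziness would not be Severe. But an event that incapacitates without threatening life would not be Severe either. The wording needs repair on both readings.

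**3. Comparison with the reporting categories.** The exercise-stopping category admits events of any intensity, and the serious-event definition does not mention stopping exercise. The article therefore already keeps stopping, seriousness and severity apart. The Severe definition merges stopping back into severity. On the plain reading, events in the exercise-stopping category would qualify as Severe, so the grade would say little within that category.

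**4. Overlap with the primary endpoint.** A symptomatic stop recorded as an adverse event fixes the exercise time and also meets the Severe wording. The overlap is substantial but not complete:
- Some stops need not be adverse events: failure of monitoring equipment, a request to stop without symptoms, and possibly fatigue at a Borg score of 5, since fatigue is not among the anticipated exercise harms.
- A severe event during recovery leaves exercise time unchanged.
- The endpoint is a duration, whereas the grade is a category for each event. If VR moved stops later without preventing them, exercise time would rise and the Severe count would not change.

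**5. Where the grade is used.** It is recorded for each event. It is not used in the reporting criteria, in the escalation trigger under Serious adverse event reporting (two or more serious events potentially related to study procedures), or in the chi-square comparison of event incidence under Data analysis approach for harms.

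**6. Illustration.** The group size of 30 comes from Sample size. The stopping proportion *p*, and the share *s* of stops recorded as adverse events, are assumptions. The number qualifying as Severe through the stopping alternative is 30 × *p* × *s*.
- *s* = 1: 30 × 0.20 = 6 and 30 × 0.40 = 12.
- *s* = 0.5: 30 × 0.20 × 0.5 = 3 and 30 × 0.40 × 0.5 = 6.
- If 40% of controls and 20% of VR participants stopped early, the contrast would be 12 against 6 when *s* = 1 (12/30 − 6/30 = 20 percentage points). It would be 6 against 3 when *s* = 0.5 (10 points).

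Each contrast is the difference in early stopping multiplied by *s*. It carries no separate information about clinical intensity.

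**The case against.** The strongest reply is that the three grades share one form, a leading descriptor followed by qualifiers. If Mild is read as a joint description, Severe should be too, and its leading word is incapacitating. A cramp that clears in a minute is not incapacitating. An event that prevents continuation may also differ from one that triggers a rule-based stop. This stands in part: the semicolons are ambiguous, so it goes too far to say that every session-ending adverse event is Severe by rule. But an explicit alternative sits inside the Severe wording, nothing elsewhere narrows it, and the joint reading leaves the gap shown in step 2.

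The second reply is that no planned comparison or safety decision uses severity. That is correct and limits the consequence. It does not rescue a grade that must be recorded and cannot be interpreted consistently.

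A reader might go further and infer that severity is simply a second count of the primary outcome, that longer exercise with VR must produce fewer Severe events, or that truly dangerous events would be hidden among routine stops. The documents do not support this. The endpoint is a time, not every stop is an adverse event, and serious events are defined and reported separately without reference to stopping.

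**Conclusion.** The Severe definition is faulty as written and should be corrected. On its plain reading it gives a brief, self-resolving, session-ending symptom two incompatible grades, and it ties the top grade to symptom-driven stopping. Any between-arm display of severity would tend to follow early stopping and would dilute clinically severe events.

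The size is modest. Only the recorded severity grade is affected. The primary analysis, the incidence test, the serious-event definition and the escalation trigger are untouched. The figures of 6 to 12 per arm rest on assumed stopping rates of 20% to 40% with every such stop recorded as an adverse event. They are illustrative, and no severity table of that kind is planned in the article.

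**What to change.** Delete the stopping-exercise alternative from the Severe grade, so that severity rests on clinical intensity and consequence. State that the remaining Severe descriptors are alternatives and that the highest grade met applies. The precedence rule alone would not be enough: with the clause still in place, it would settle the test case as Severe.

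Add a yes/no field to the case report form for whether the event led to session termination, and use it to feed the existing exercise-stopping category. Trial status dates the start of recruitment to 10 November 2025, so any events already recorded should be regraded under the corrected definition.

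The cost is one deleted clause, one added sentence, one form field and a short regrading exercise, handled through the protocol's amendment procedure where required. The discontinuation criteria stay as they are.
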